#### Individuals who have been offered but not received ICJ

A stratified sample based on gender, age, cancer type and socio-demographic band will be developed based on the ‘individuals who have used ICJ’ sample. The service will also post the study pack on behalf of the research team to this sample alongside a reminder that ICJ is still available to them should they so wish.

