### Analysis

*Objective 1 - Identify the impact of ICJ on those diagnosed with cancer*

Hypotheses are:Individuals who have engaged with ICJ will report significantly different mean scores on patient activation measures than those who have not.Individuals who have engaged with ICJ will report significantly different mean scores on quality of life measures than those who have not.Individuals who have engaged with ICJ will report significantly different mean scores on social support than those who have not.Self -reported experience of ICJ will be significantly associated with scores on quality of life measures, patient activation scores and support.

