#### Power analysis

There is no evidence to support effect size estimates so a moderate effect size of ICJ (d = 0.5) was adopted. Alpha was set to 0.0167 to allow for testing three different hypothesised mean differences (Hypotheses 1–3) on the same samples. With power set at 95 % this returned an estimated required total sample size of 264 (132 in each group) using G*Power version 2.

For the fourth hypothesis (self-reported experience of ICJ will be associated with scores on quality of life measures, patient activation scores and support) we ran an exact test on G*Power (version 2) running a correlation: bivariate model with the following assumptions: one tailed, hypothesised correlation 0.3, alpha error .05, power 95 %. This returned a sample size of 115. Whilst we hope to obtain a larger sample in order to conduct subgroup analyses, the required sample appears achievable.

The data will first be tested for outliers using boxplots and for normality using QQ plots. If normality is found, homogeneity of variance between groups will be tested with Levene’s test. Subsequent calculations will be based on the outcomes of these assumption tests. If normality and homogeneity of variance are established mean scores (from the PAM-13, FACT-G, EQ5-D and the MOS Social Support Survey) will be compared between the ICJ and non-ICJ group using *t*-test. If normality and/or homogeneity of variance cannot be established, a corresponding nonparametric method will be employed.

*Objective 2: To understand the process of ICJ as experienced by:*○ Patients and carers in receipt of the service○ The service providers, and○ The wider culture

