This protocol has limitations. We acknowledge Glasgow’s distinctive demography and the impact this may have on the generalizability of the findings. This is why we have proposed to evaluate the service from three levels; patient/carer, link officer and wider stakeholders to examine both individual and cultural factors to determine what factors are unique to the local area, what elements may be transferable and how this corresponds to wider findings relating to how and why this service may improve the lives of those affected by cancer. For comparative purposes we will distribute the questionnaire to a matched sample of individuals who also live in Glasgow, have been offered the ICJ service but decided not to take it up. As this sample live in Glasgow it minimizes any possible confounding variables from, for example, recruiting individuals who are cared for under a different health board. We hypothesise that those who have used the service with have significantly better outcomes than those who have not. However, we do not know why this group of individuals decided not to take up the service. It is possible that they are already well supported meaning there will be no difference in their outcomes. We will explore their reasons for not taking up the service along with descriptive statistics to provide further context to these findings.

Health policy in many countries has prioritised detecting and screening for psychological needs relating to cancer. Yet, despite this, distress is very common in those affected by cancer, across diagnoses and the disease trajectory. This service takes a proactive approach to screening drawing on a psychosocial holistic model of care to offer everyone in the city of Glasgow a personalised assessment right from diagnosis until whatever point that individual decides they no longer require the support. It is this element of care that is unique. The personalised approach provided by the link officers is at the centre of this service. Consequently, a key part of this research will focus on their experiences delivering the service. This will gather evidence that highlights how their skills and interactions with their clients shape the service but also how the service managers can support the link officers. This may be through the identification of training needs or recognition of the need to incorporate regular supervision into their working pattern to cope with the demands of working in an emotionally charged environment.

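### The only stated Objective 1 comparison is unadjusted between people who took up ICJ and people who did not, and it leaves out the four variables used to build the comparison sample

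*Protocol article*

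**What the plan says.** The Aim and objectives section makes the impact of ICJ on people diagnosed with cancer the first objective. The Eligibility criteria define the user group as people who have already had a holistic needs assessment with ICJ. The comparison group is people with cancer who were offered ICJ and did not take it up, whatever the reason.

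For recruitment of the comparison group, "A stratified sample based on gender, age, cancer type and socio-demographic band will be developed" from the profile of the user sample. The Discussion calls this sample matched.

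Under Power analysis, the scores from PAM-13, FACT-G, EQ-5D and MOS-SSS "will be compared between the ICJ and non-ICJ group using" a t-test when normality and equal variances hold, and a corresponding nonparametric method otherwise. No covariate, stratum, matched set or weight is named for either branch.

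On selection, the Discussion says: "However, we do not know why this group of individuals decided not to take up the service". It adds: "It is possible that they are already well supported meaning there will be no difference in their outcomes". The planned response is to explore the reasons for non-uptake and to present descriptive statistics as context.

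**The concern.** Exposure to ICJ is chosen by the participant. A raw difference in mean scores between those who took up the service and those who did not therefore combines any effect of ICJ with differences in case-mix, need and existing support. No pre-service score is described for users, so the comparison cannot be anchored to a baseline either.

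The protocol treats four variables as important enough to sample on, and then leaves them out of the analysis. Sampling on them gives some balance among the people who are sent a pack, but the analysis uses those who return one. If response differs between the groups, that balance may be lost. An independent-samples t-test would not correct this, and it would not use the strata to reduce residual variance.

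The one selection mechanism that the protocol names, good existing support among decliners, bears directly on MOS-SSS, which is itself an outcome under Hypothesis 3. Neither exploring reasons nor descriptive statistics changes the test on which the Objective 1 conclusion would rest. The results are meant to inform commissioning and possible replication elsewhere, so a difference, or the lack of one, could be wrongly credited to the service.

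**Working it through.** **Inputs from the Power analysis section.**
- Alpha: "Alpha was set to 0.0167 to allow for testing three different hypothesised mean differences (Hypotheses 1–3) on the same samples".
- Effect size: "There is no evidence to support effect size estimates so a moderate effect size of ICJ (d = 0.5) was adopted".
- Power and size: "With power set at 95 % this returned an estimated required total sample size of 264 (132 in each group").
- Sidedness is not stated for Hypotheses 1 to 3. It is taken as two-sided because the hypotheses are non-directional (for example, users "will report significantly different mean scores on patient activation measures than those who have not").

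**Reproducing the plan's figure.** For a two-sample t-test with n per group, the degrees of freedom are 2n − 2 and the noncentrality is d × √(n/2). With n = 132 there are 262 degrees of freedom, the critical value at two-sided 0.0167 is 2.409, and √(132/2) = 8.124. For d = 0.5 the noncentrality is 0.5 × 8.124 = 4.062 and power is 95.0%. This is the smallest n that reaches 95%, so the total is 264, an exact match. A one-sided test at the same alpha gives 230, which does not match. The sample-size arithmetic is sound. It treats the whole difference of 0.5 SD as the effect of ICJ.

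**What a selection difference does to the stated test.** Let b be a group difference, in SD units, that is not due to ICJ. The documents give no value for b, so a range is assumed. The observed difference is d + b, and the rejection probability is the two-sided noncentral-t power at that value, with n = 132 per group.

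| Observed difference (SD) | Noncentrality | Chance of a significant result |
|---|---|---|
| 0 | 0 | 1.7% |
| 0.1 | 0.812 | 5.7% |
| 0.2 | 1.625 | 21.9% |
| 0.3 | 2.437 | 51.2% |
| 0.4 | 3.250 | 79.9% |
| 0.5 | 4.062 | 95.0% |

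- *No ICJ effect (d = 0).* The observed difference equals b, so the table gives the false-positive rate per hypothesis: 21.9% for b = 0.2 and 51.2% for b = 0.3, against a nominal 1.67%.
- *True d = 0.5 with selection against users.* The observed difference is 0.5 − |b|. Power falls to 79.9% for |b| = 0.1, 51.2% for 0.2 and 21.9% for 0.3.
- *Larger sample, which the protocol hopes for.* With b = 0.2 and no effect, the false-positive rate is 52% at 300 per group and 86% at 600 per group. More data do not remove bias.

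**Whether adjustment fits the planned size.** An adjusted comparison needs a total of about 264 × (1 − R²outcome) / (1 − R²group). R²outcome is the share of outcome variance explained by the covariates, and R²group is the share of group membership they explain. Neither is in the documents. Over assumed ranges of 0 to 0.3 and 0 to 0.2, the extremes are 264 × 0.7 / 1 ≈ 186 (rounded up to equal groups) and 264 × 1 / 0.8 = 330.

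**The case against.** **The protocol already addresses the four variables in sampling.** This stands in part. Stratification should make them the smaller source of bias, and no response rates or respondent profiles are given, so loss of balance after mailing is plausible but not established. It remains true that the test would not correct an imbalance if one arose, and that it does not use the strata.

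**The figures do not measure the omitted adjustment.** This stands. They show what a total selection bias of a given size would do. Existing support and need are not among the four variables, so adjustment may leave much of that bias in place.

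**The limitation is disclosed.** This stands as far as it goes. The Discussion raises selection openly, and understanding non-uptake is one of the two stated reasons for including this sample. But no analysis or restriction on wording follows from it.

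**A condensed article may leave adjusted analyses to a fuller plan.** Further analyses may exist. The main test and its fallback are nevertheless stated here and the study is powered on that comparison, so this is a choice made and not a detail omitted.

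Three stronger readings are tempting and not supported. A reader might infer that confounding would produce a false benefit; the protocol's own scenario of well-supported decliners would instead hide one, and the direction is unknown. A reader might take the remark about Glasgow residence as a claim that confounding has been dealt with; that sentence concerns differences such as being cared for under another health board. And a reader might conclude that adjusting for the four variables would isolate the effect of ICJ; it would not.

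**Conclusion.** The point holds. As stated, the Objective 1 analysis is an unadjusted comparison of self-selected groups that discards the variables used to construct the comparison sample, and it cannot by itself support a statement about the impact of ICJ. Selection may create a difference or mask one.

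The size is not known from the documents. For illustration, if the total selection bias were 0.2 SD, the chance of a false positive per hypothesis would be 22% instead of 1.67%, or power for d = 0.5 would fall from 95% to 51% if the bias opposed the effect. These figures assume 132 respondents per group, a two-sided test at 0.0167 and equal variances. They are not an estimate of what adjustment would recover. The planned sample size reproduces exactly and is not in question.

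**What to change.** Make the main Objective 1 analysis a linear regression of each score on ICJ status, adjusted for gender, age, cancer type and socio-demographic band. Add time since diagnosis or since the offer only if it is recorded for both groups; the documents do not show that it is. Report the adjusted mean difference with its confidence interval and keep the raw comparison as descriptive. Word the results as adjusted associations between uptake and outcome and not as impact, because need and existing support remain unadjusted.

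The statistical cost is a few degrees of freedom, and adjustment is feasible at about the planned size under the ranges assumed above. The practical cost is that the four variables must be attached to each returned questionnaire. For people who did not take up ICJ, the service posts the packs on the research team's behalf, and the consent to share data described for users is given at the needs assessment, which this group did not have. The plan therefore needs either a study ID that permits linkage to the sampling frame for both groups, or the four items asked in the questionnaire itself.

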### Aim and objectives

The overarching aim of this study is to understand if and how ICJ impacts upon the experiences of people living with and affected by cancer. There are 2 objectives:To identify the impact of ICJ on those diagnosed with cancerTo understand the process of ICJ as experienced by○ Patients and carers in receipt of the service○ The service providers, and○ The wider culture.

Hypotheses are:Individuals who have engaged with ICJ will report significantly different mean scores on patient activation measures than those who have not.Individuals who have engaged with ICJ will report significantly different mean scores on quality of life measures than those who have not.Individuals who have engaged with ICJ will report significantly different mean scores on social support than those who have not.Self -reported experience of ICJ will be significantly associated with scores on quality of life measures, patient activation scores and support.

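### The nonparametric fallback drops the hypothesis about means and does not remedy unequal variances; a Welch comparison of means avoids both problems

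*Protocol article*

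**What the plan says.** Hypotheses 1–3, given under Aim and objectives and again under Analysis, are about means, for example "Individuals who have engaged with ICJ will report significantly different mean scores on patient activation measures than those who have not". The Power analysis section is built on the same quantity. It assumes a standardised mean difference ("a moderate effect size of ICJ (d = 0.5) was adopted"), and it sets the significance level for mean differences: "Alpha was set to 0.0167 to allow for testing three different hypothesised mean differences (Hypotheses 1–3) on the same samples".

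The same section then fixes how the test is chosen. Outliers are checked with boxplots and normality with QQ plots. The variance check comes second and is conditional: "If normality is found, homogeneity of variance between groups will be tested with Levene’s test". If both assumptions are established, the means of PAM-13, FACT-G, EQ-5D and the MOS social support survey are compared by t-test. Otherwise: "If normality and/or homogeneity of variance cannot be established, a corresponding nonparametric method will be employed". The nonparametric method is not named, and no t-test that allows unequal variances is mentioned.

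**The concern.** The stated rule does not serve the stated hypotheses, for three reasons.

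- **It changes the question.** A rank test for two independent groups addresses the probability that a member of one group scores above a member of the other. That is not a difference in means unless the two distributions have the same shape and spread. The check is applied score by score, so one outcome could be judged on means and the next on ranks, depending on how a QQ plot looks.
- **It does not treat unequal variances.** The rule sends data to the rank test even when the only failure is unequal variance. Mann-Whitney takes its null variance from identical distributions, which is exactly what a failed Levene test puts in doubt.
- **It is hardly needed.** At the planned 132 per group, a comparison of means tolerates moderate skewness of the raw scores. Unequal variances can be handled while still comparing means.

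At stake is whether a significant result answers Hypotheses 1–3, and whether 0.0167 is the actual error rate for a mean difference.

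**Working it through.** **Step 1. Reproduce the planned size.** Inputs from the Power analysis section: d = 0.5, alpha = 0.0167, power 95%. Sidedness is not stated; a hypothesis of a difference without direction implies two-sided. For n per group, df = 2n − 2 and the noncentrality parameter is d·√(n/2). At n = 132, df = 262 and the noncentrality is 0.5 × √66 = 4.06. The two-sided noncentral-t power is 0.9502, and 132 is the smallest n that reaches 95%. This reproduces "With power set at 95 % this returned an estimated required total sample size of 264 (132 in each group) using G*Power version 2". A one-sided test would need only 115 per group (230 in total). The planned size is therefore that of a two-sided t-test on means.

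**Step 2. Identify the branches.** Levene's test is run only when normality is accepted. The rank test is reached in two ways: (a) near-normal data with unequal variances; (b) non-normal data, whatever the variances. They need separate checks.

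**Step 3. Why the error rate can move.** Mann-Whitney uses z = (U − n₁n₂/2) / √(n₁n₂(n₁ + n₂ + 1)/12). With symmetric data and equal means, the centre n₁n₂/2 is right, but the variance is wrong when the spreads differ. The direction of the error depends on which group is larger. With skewed data and unequal spreads, the centre moves too, because P(X > Y) is no longer 0.5 although the means are equal.

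**Step 4. Branch (a), normal data.** Setup: equal means, two-sided 0.0167, 20,000 replicates. The Monte Carlo standard error is √(0.0167 × 0.9833 / 20,000) = 0.0009. SD ratios and group splits are assumptions. Unequal groups are plausible because the Recruitment section invites every eligible service user but only a stratified sample of non-users. Rejection rates in %, Mann-Whitney with Welch in brackets:

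| Group sizes | SD ratio 1.25 | 1.5 | 2 |
|---|---|---|---|
| 132 / 132 | 1.55 (1.46) | 1.74 (1.54) | 2.16 (1.60) |
| 88 / 176, smaller group more variable | 2.04 (1.55) | 2.56 (1.65) | 3.47 (1.48) |
| 66 / 198, smaller group more variable | 2.51 (1.93) | 3.21 (1.67) | 4.39 (1.63) |
| 176 / 88, larger group more variable | 1.37 (1.71) | 1.15 (1.74) | 0.99 (1.68) |
| 198 / 66, larger group more variable | 1.12 (1.74) | 0.74 (1.59) | 0.61 (1.64) |

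With 264 and 132 and an SD ratio of 2, Mann-Whitney rejected in about 3.7% when the smaller group was more variable and 0.8% when the larger group was.

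**Step 5. Branch (b), skewed data.** Setup: scaled-beta scores on an assumed 0–108 range, equal means, 10,000 to 20,000 replicates. Ranges show repeat runs.

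- Mean 80, SD 15 vs 22: Mann-Whitney 10.8–11.2% at 132/132 and 16.2–17.3% at 264/132; Welch 1.7–1.9%.
- Mean 75, SD 15 vs 20: 3.8% at 132/132 and 5.3–5.9% at 264/132; Welch 1.6–1.9%.
- Mean 80, SD 15 vs 17, 132/132: 2.1%. With equal SDs: 1.4%.
- Mean 60, SD 15 vs 20, 132/132: 1.6%, as the score is then close to symmetric.

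A more strongly skewed shape (reflected gamma, shape 2) at 132/132 gave 5.5%, 13.2% and 28.3% at SD ratios 1.25, 1.5 and 2, with Welch at 1.7–1.8%. Across all gamma scenarios Welch ranged from 1.5% to 2.3%, the highest at 66/198 with SD ratio 2.

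**Step 6. Cost of always using Welch.** With equal variances, d = 0.5 and 132 per group, simulated power was 95.2% for both Welch and the pooled t-test.

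**The case against.** The strongest reply is that the rule does little harm in the planned setting. Levene's test is reached only with near-normal data, and there, at 132 per group, Mann-Whitney stays close to 1.67%. A reader might infer from the text that the fallback inflates the false-positive rate in general. The figures do not support that: the rate can be near nominal, too high or too low, depending on group sizes and skewness. The large excess needs skewed scores, clearly unequal SDs and exactly equal means, none of which the document specifies. Part of that excess is Mann-Whitney correctly detecting a difference in P(X > Y). It is thus largely another view of the changed hypothesis, not a separate defect. All of this stands.

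It is also fair that the method is unnamed; Mann-Whitney is the natural reading, not a stated choice. Two further inferences have no basis in the text. One is that no mean difference or confidence interval would be reported: the article is silent, and such detail is commonly left to fuller documents. The other is that the fallback would usually be the actual analysis, which rests on assumed ceiling effects.

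What the reply does not meet is the mismatch itself. The switch away from means is a rule written in the protocol, not a detail left open.

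**Conclusion.** The point holds in this form: the fallback abandons the mean differences on which Hypotheses 1–3 and the sample size rest, and it does not reliably control the error rate for a mean difference when variances are unequal. The mismatch of hypothesis and test needs only the protocol's own wording and the natural reading of the unnamed method as Mann-Whitney.

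The size of the error depends on assumptions about SDs, score shapes and group sizes. Against a nominal 1.67% it is about 1.6–2.2% for normal data at 132/132. At SD ratio 2 with 2:1 groups it is about 0.8% or 3.7%, according to which group is more variable. For the bounded, skewed scores with unequal SDs it is about 2–16%. Welch stayed near nominal in the same settings. The stated sample size is correct and is not affected.

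**What to change.** Delete the normality and Levene gate. For each of the four scores, state in advance that group means will be compared by Welch's t-test, reported as a mean difference with a confidence interval. An equivalent linear model with heteroscedasticity-robust standard errors would also do, though it was not simulated here. QQ plots and boxplots can stay as description. Mann-Whitney, named as such, can be kept as a sensitivity analysis for every score, with the statement that it addresses a different quantity.

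The cost is a change of wording in the analysis text. The total of 264 stands, and the loss of power with equal variances is negligible.
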